## Abstract

**Background:**

Intramuscular injection of botulinum toxin type-A given by manual intramuscular needle placement in the lower extremity under general anaesthesia is an established treatment and standard of care in managing spasticity in children with spastic cerebral palsy. Optimal needle placement is essential. However, reports of injection and verification techniques used in previous studies have been partly incomplete and there are methodological shortcomings. This paper describes a detailed protocol for manual intramuscular needle placement checked by passive stretching and relaxing of the target muscle for each individual muscle injection location in the lower extremity during botulinum toxin type-A treatment under general anaesthesia in children with spastic cerebral palsy. It explains the design of a study to verify this protocol, which consists of an injection technique combined with a needle localizing technique, as by means of electrical stimulation to determine its precision.

**Methods:**

Setting: University Medical Centre, Department of Paediatric Rehabilitation Medicine, the Netherlands.

Design: prospective observational study.

Participants: children with spastic cerebral palsy, aged 4 to 18 years, receiving regular botulinum toxin type-A treatment under general anaesthesia to improve their mobility, are recruited from the Department of Paediatric Rehabilitation Medicine at VU University Medical Centre, Amsterdam, the Netherlands.

Method: a detailed protocol for manual intramuscular needle placement checked by passive stretching and relaxing of the target muscle has been developed for each individual muscle injection location of the adductor brevis muscle, adductor longus muscle, gracilis muscle, semimembranosus muscle, semitendinosus muscle, biceps femoris muscle, rectus femoris muscle, gastrocnemius lateralis muscle, gastrocnemius medialis muscle and soleus muscle. This protocol will be verified as by means of electrical stimulation.

Technical details: 25 mm or 50 mm Stimuplex-needle and a Stimuplex-HNS-12 electrical stimulator will be used.

**Discussion:**

Botulinum toxin type-A injected in the intended muscle is expected to yield the greatest effect in terms of activities. Protocols for manual intramuscular needle placement should be described in detail and verified to determine its precision. Detailed and verified protocols are essential to be able to interpret the results of botulinum toxin type-A treatment studies.

## Background

Cerebral palsy (CP) is defined as a disorder of posture and movement due to a defect or lesion in the immature brain [1]. It causes physical and movement disability in childhood with an annual incidence of 2 to 3 per 1000 live born children [1,2]. It is a non-progressive motor disorder. The type of movement disorder is classified as spastic, ataxic, dyskinetic, or a combination. To manage spasticity in children with spastic cerebral palsy botulinum toxin type-A (BTX-A) injected by manual intramuscular needle placement in the lower extremity under general anaesthesia is an established treatment and standard of care in children with spastic CP [3-6].

BTX-A is produced by the bacterium Clostridium botulinum, and blocks the release of acetylcholine at the neuromuscular junction. This chemodenervation causes temporary focal weakness of the injected muscle. Over a period of weeks to months, collateral sprouting of the nerve results in reinnervation of the muscle, which results in recovery of the neuromuscular junctions [7-15].

There are various intramuscular injection techniques and needle localizing techniques to administer BTX-A treatment. Location of the needle after manual intramuscular needle placement can be checked by passive stretching and relaxing of the target muscle (PSRM) [16-21], palpation [18,21] and imaging and guiding tools: electrical stimulation (ES) [16,18,21-23], ultrasound [19-21,23,24], computer tomography, X-ray [14,16,17,19,22,24,25] and electromyography [17,19,22].

PSRM is a rapid intramuscular needle localization technique, useful for larger muscles, especially in the lower extremity, which can be performed by one doctor and one assistant without sophisticated equipment.

The selection of muscles to be injected depends on the limitations the patient experiences in some activities due to abnormal activation and activity of the muscles. Injecting BTX-A at the correct location in the intended muscle is expected to yield the greatest effect in terms of activities. Therefore locating the right muscle is an important part of the treatment. Protocols of intramuscular needle placement and intramuscular needle placement verification techniques should be described in detail and verified to determine its precision. Detailed and verified protocols are essential to be able to interpret results of BTX-A treatment studies.

To evaluate previous research on this topic, the literature was searched from the first relevant article on this topic in 1994 to April 2013 using Pubmed, Cochrane database and references of related articles. Keywords used were needle placement, botulinum toxin type-A, cerebral palsy, muscle, electrical stimulation, children, spasticity, injections, echo and ultrasound. MeSH headings used were botulinum toxin type-A, needle, cerebral palsy, muscle spasticity, children, injections, muscle. All languages were included.

In a recent randomised controlled trial, two botulinum toxin injection techniques were compared on the functional improvement of the leg of children with CP. The efficacy of BTX-A treatment was compared between intramuscular injections guided by electrical stimulation and intramuscular injections guided by palpation. The treatment groups received two weeks of physiotherapy after BTX-A treatment. A third group received physiotherapy without BTX-A treatment. The paper reported that intramuscular injection of BTX-A guided by electrical stimulation plus physiotherapy was likely to be best in terms of improving functional performance and spasticity [18]. A similar study compared “free hand” intramuscular needle placement guided by anatomic landmarks, palpation and passively stretching of the muscles with intramuscular needle placement guided by electrical stimulation. “Free hand” manual intramuscular needle placement was found to be acceptable only for the gastrocnemius and soleus muscles (75%) and unacceptable for all the other muscles investigated [16]. A comparative study described intramuscular needle placement guided by ultrasound for the gastrocnemius muscle. The accuracy of the manual needle placement into the medial head was found to be satisfactory, but the accuracy of the lateral head placement was disappointing [21].

The present study describes a detailed protocol for manual intramuscular needle placement in the lower extremity checked by PSRM for each individual muscle injection location during botulinum toxin type-A treatment under general anaesthesia in children with spastic cerebral palsy (see Additional file 1). It explains the design of a study to verify this protocol, which consists of an injection technique combined with a needle localizing technique, as by means of ES and calculates its precision.

## Methods/Design

### Methods

A detailed protocol for manual intramuscular needle placement checked by PSRM has been developed for each individual muscle and its injection locations of the adductor brevis muscle (ADB), adductor longus muscle (ADL), gracilis muscle (GR), semimembranosus muscle (SEM), semitendinosus muscle (SET), biceps femoris muscle (BF), rectus femoris muscle (RF), gastrocnemius lateralis muscle (GL), gastrocnemius medialis muscle (GM) and soleus muscle (SO) (see Additional file 1). This protocol describes the origin, the insertion, the relationship to other structures, the innervation and function of the muscle. It explains the start position of the patient at physical examination for injection, how to support and fixate the leg and the skills to localise the muscle belly and the different injection locations of the target muscle. It clarifies the direction of the needle, the intramuscular needle placement technique and explains the way to check the correct intramuscular needle location by PSRM. It also shows needle placement hazards for each muscle separately.

This protocol, which consists of a manual intramuscular needle placement technique combined with a needle localizing technique, will be verified as by means of ES to determine its precision.

### Design

This is a prospective observational study.

Approval was obtained from the Medical Research Ethics Committees of the Medical Centre, Amsterdam, the Netherlands and MOVE Research Institute Amsterdam of the VU University Medical Centre, Amsterdam, the Netherlands. This study is in compliance with the Helsinki Declaration. The research will be conducted according to the 2004 version of the principles of the Declaration of Helsinki and in accordance with the Dutch Medical Research Involving Human Subjects Act (WMO). Risks associated with participation and physical discomfort are very small to negligible, and participation is not associated with greater physiological discomfort compared to regular BTX-A treatment [9,11,26-30].

### Setting

University Medical Centre, Department of Paediatric Rehabilitation Medicine, the Netherlands.

### Participants

Children with spastic cerebral palsy, aged 4 to 18 years, receiving regular BTX-A treatment under general anaesthesia to improve their mobility, will be recruited from the Department of Paediatric Rehabilitation Medicine, VU University Medical Centre, Amsterdam, the Netherlands.

Inclusion criteria:

1. Children aged 4 to 18 years

2. Diagnosis of spastic CP

3. Planned for regular BTX-A treatment under general anaesthesia

4. Informed consent from caregivers and child if capable

Exclusion criteria:

1. Risk > 2 of the American Society of Anesthesiologists (ASA) physical status classification system during anaesthesia

2. Previous surgery of the muscles included in the study

3. Concomitant muscle-related diseases

4. Infection at the location of needle placement

### Sample size calculation

Each individual muscle injection location of the ADB, ADL, GR, SEM, SET, BF, RF, GL, GM and SO after manual intramuscular needle placement checked by PSRM will be investigated by ES to determine correct needle placement.

The positive predictive value (PPV) or precision is clinically the most relevant parameter to assess the value of this manual intramuscular needle placement checked by PSRM, as it indicates the proportion of the true positive needle placements in the intended muscle against all, true and false, positive needle placements in the intended muscle. If we assume that 90% of the test outcome of manual intramuscular needle placements observed after PSRM is determined to be positive, with α = 0.05 and a power of 80%, then 41 observations of a positive manual intramuscular needle placement will be required for the injection location for each individual muscle. If we assume that approximately 70% of the test outcome of manual intramuscular needle placements observed after PSRM is determined to be positive, with α = 0.05 and a power of 80%, then a total of 60 observations of a positive manual intramuscular needle placement will be required for the injection location for each individual muscle.

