### Statistical analysis

Analyses will be performed using the Statistical Package for the Social Sciences, version 15.0 (SPSS, IBM, New York, USA). The main object of the analysis will be the contingent table of manual intramuscular needle placement checked by PSRM observations versus the corresponding verification as by means of ES observations (see Table 1). This table will be used to calculate the positive predictive value (PPV), with its confidence interval of 95%, as the main objective for each individual muscle and muscle injection location. Positive predictive value or precision is defined as the proportion of the PSRM true positive observations against all the positive observations, both PSRM true positive and PSRM observations. A PPV of 80% with 95% confidence interval and a lower bound of 70% is defined as a minimal acceptable proportion. In addition, negative predictive value (NPV), sensitivity and specificity will also be computed, with their confidence intervals of 95%.

**Table 1 T1:** Contingent table of manual intramuscular needle placement checked by PSRM observations versus the corresponding observations with ES

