Additional file 1 provides no guidance of manual intramuscular needle placement depth because it is complicated. The recruited children are aged between 4 and 18 years old and needle depth might depend on the child, age, muscle type, muscle injection location, left and right legs, gender, height, weight and body mass index.

This protocol for manual intramuscular needle placement checked by PSRM is described in detail. If verification of this protocol as by means of ES shows a minimal precision or PPV of 80% with 95% confidence interval and a lower bound of 70% then this protocol is precise and suitable for use in clinical practice of BTX-A treatment in children with spastic cerebral palsy in the lower extremity.

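### The targets of 41 and 60 positive placements are tied to the PSRM-positive share rather than to an assumed PPV, so the stated 80% power is not shown for the PPV success rule

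*Protocol article*

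**What the plan says.** The Sample size calculation section names the PPV as the clinically most relevant parameter. It then gives two conditional statements, both at α = 0.05 and 80% power.

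- First condition: "If we assume that 90% of the test outcome of manual intramuscular needle placements observed after PSRM is determined to be positive". Result: "then 41 observations of a positive manual intramuscular needle placement will be required for the injection location for each individual muscle".
- Second condition: "If we assume that approximately 70% of the test outcome of manual intramuscular needle placements observed after PSRM is determined to be positive". Result: "then a total of 60 observations of a positive manual intramuscular needle placement will be required for the injection location for each individual muscle".

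The section gives no null PPV, no assumed true PPV, no test and no sidedness. It does not say which of the two numbers governs a given location.

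The success rule stands elsewhere. The Statistical analysis section says: "A PPV of 80% with 95% confidence interval and a lower bound of 70% is defined as a minimal acceptable proportion". The Discussion attaches the conclusion to that rule, for the case that verification "shows a minimal precision or PPV of 80% with 95% confidence interval and a lower bound of 70% then this protocol is precise". It adds that clinical use would then be appropriate. Table 1 and its legend define the PPV as true positives over all PSRM-positive placements.

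**The concern.** The assumed percentages describe how often PSRM is positive. The PPV is estimated among PSRM-positive placements only, so once the target is a number of positives, the positive share has no further part in the precision or power for the PPV. The text nevertheless raises the required positives from 41 to 60 as the share falls from 90% to about 70%.

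Reading the percentages as assumed PPVs does not repair this, because 70% is the value that the lower confidence bound has to reach.

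What is at stake is how each location's result is read. A location that misses the rule would be taken to have failed a test with 80% power, although the plan does not say at what true PPV that power applies.

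**Working it through.** **Inputs.** α = 0.05 and power 80% (Sample size calculation). Two-sided α is assumed because the rule uses a 95% interval. Targets 41 and 60 (same section). Rule: observed PPV at least 80% and lower 95% bound at least 70% (Statistical analysis, Discussion). The true PPV is not stated, so it is varied from 70% to 90%. Placements are treated as independent.

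**1. Trying to reproduce 41 and 60.** The stated inputs alone give no sample size. Borrowing the 70% bound as the null and 90% as the true PPV:

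- Null-variance formula: n = (1.96 + 0.84)² × 0.70 × 0.30 / 0.20² = 41.2, close to 41 (42 if rounded up).
- Score formula: n = [(1.96√0.21 + 0.84√0.09) / 0.20]² = 33.1.

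So 41 is near one version of a 70% versus 90% test. On the same footing 60 does not appear, since a true PPV of 70% against a null of 70% leaves no difference to detect. 60 does appear as a total: 42 / 0.70 = 60.0. The same division in the other scenario gives 42 / 0.90 = 46.7, not 41. One figure therefore looks like a count of positives and the other like a count of all placements, while the text calls both positives.

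**2. What the positive share can do.** Total placements = positives / share.

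| PSRM-positive target | Total at 90% share | Total at 70% share |
|---|---|---|
| 41 | 41/0.9 = 45.6, i.e. 46 | 41/0.7 = 58.6, i.e. 59 |
| 60 | 60/0.9 = 66.7, i.e. 67 | 60/0.7 = 85.7, i.e. 86 |

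The PPV denominator stays at 41 or 60 in each row.

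**3. Pass mark.** The smallest number of true positives r that meets both parts of the rule. The lower-bound condition decides r in every case below.

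- n = 41: r = 35 (Wilson 35/41 gives 0.716 and 34/41 gives 0.687; Clopper-Pearson 0.708 and 0.679). Wald: r = 34.
- n = 60: r = 50 for Clopper-Pearson (0.715; 49/60 gives 0.696). r = 49 for Wilson (0.701) and Wald (0.719).

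**4. Pass probability.** P(X ≥ r) for X ~ Binomial(n, true PPV).

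| n, pass mark | Interval | PPV 70% | 80% | 85% | 90% |
|---|---|---|---|---|---|
| 41, r = 35 | Wilson, Clopper-Pearson | 1.9% | 26% | 58% | 89% |
| 41, r = 34 | Wald | 4.6% | 41% | 73% | 95% |
| 60, r = 50 | Clopper-Pearson | 1.4% | 32% | 72% | 97% |
| 60, r = 49 | Wilson, Wald | 2.9% | 45% | 82% | 98.5% |

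Solving P(X ≥ r) = 0.80 for the true PPV gives 0.883 (35/41), 0.861 (34/41), 0.862 (50/60) and 0.847 (49/60).

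**5. Percentages read as PPVs.** With 41 positives at 90% the pass probability is 89–95%. With 60 positives at 70% it is 1.4–2.9%. Neither scenario carries the same 80%.

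**The case against.** The strongest reply is that the section names no true PPV, so its power cannot be called false. At a true PPV of 90% both targets exceed 80% against the 70% bound, and 60 positives give 82% at 85% under Wilson. A derivation from 70% versus 90% may lie behind 41, and 60 may be total placements mislabelled as positives; an article may leave such detail to the full protocol. This stands in part. A reader might infer that the 80% power simply does not hold, and the document does not support that: the power is unstated as to PPV, and it is met at 90%. The hidden derivation is inference, however. One conversion does not explain both figures, and the printed text would still need correcting.

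A second reply is that low power at a true PPV of exactly 80% is partly built into the rule. If the observed PPV must itself reach 80%, the chance of that at a true PPV of 80% is only a little above one half (56% at n = 100, 52% at n = 1000), and studies are not usually powered at their own pass mark. This also stands. The 26–45% figures show how the rule behaves; they do not show that the study must be powered at 80%. It would likewise be wrong to say that a true PPV of 70% passes 2–3% of the time at any size: under the joint rule the figure is 0.3% at n = 155.

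Third, each location's PPV is reported with its interval, so imprecision will be visible. That limits the harm but does not remove it, because the Discussion turns the rule into a judgement of suitability. A reader might also infer that a location could stop at either target. The article describes no interim look or stopping rule, and the two numbers read more naturally as planning scenarios. What is missing is a statement of which one applies.

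**Conclusion.** The point holds in limited form. The section makes the required positives depend on a quantity that cannot affect them. It states neither a null nor an assumed PPV, and its two targets do not follow from one rule as counts of positives. The 80% power is therefore not shown for the success rule. For that rule it is reached only from a true PPV of about 0.86–0.88 with 41 positives and 0.85–0.86 with 60. At a true PPV of 80% a location passes 26–41% of the time with 41 positives and 32–45% with 60.

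These figures rest on exact binomial probabilities, a two-sided 95% interval and independent placements. The interval method is not named, and it moves the pass mark by one observation and the power at 85% by 10 to 15 percentage points, so no single row of the table is the definitive one. One child may contribute several placements (left and right legs are listed among the factors to be analysed); positive correlation within a child would reduce the effective sample size.

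**What to change.** Replace the two conditional sentences with one statement per location that gives:

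1. the null, a PPV of 70%, tied to the lower-bound rule;
2. the assumed true PPV;
3. the confidence interval method;
4. one of the two existing targets, labelled as PSRM-positive placements;
5. the pass mark and pass probabilities for that target and interval, at more than one true PPV;
6. the PSRM-positive rate, used only to convert to total placements (46 or 59 for 41 positives; 67 or 86 for 60);
7. the independence assumption.

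Keeping 41 changes wording only and needs no extra enrolment. With Wilson or Clopper-Pearson the text would state a pass at 35/41 or more, with power of about 89% at PPV 90%, 58% at 85% and 26% at 80%. Adopting 60 for every location is optional and is a recruitment change: 19 more positives per location than 41 (46% more). Its stated power must match the named interval: 72% at PPV 85% for Clopper-Pearson, 82% for Wilson or Wald. Either way, the stated power becomes less favourable at true PPVs near 80%.

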### Recruitment and consent

Patients with spastic CP aged 4 to 18 years, of both sexes, treated at the Department of Paediatric Rehabilitation Medicine, VU University Medical Centre, Amsterdam, the Netherlands, will be recruited by their own doctor during a consultation about regular BTX-A treatment. The caregivers and the children will be given information about the research project. A patient information letter, an explanation of the study by means of a cartoon, information about insurance issues, an informed consent form and an envelope to return the informed consent form will be handed to the caregivers at the end of the consultation. The participants will be given a telephone appointment at least 48 hours before the BTX-A treatment, to answer any questions they may have.

### Study procedures

All children will receive their planned BTX-A treatment under general anaesthesia in the operating rooms of the VU University Medical Centre. The protocol for manual intramuscular needle placement checked by PSRM will be used (see Additional file 1).

A 25 mm or 50 mm Stimuplex needle will be used for the injection. Manual intramuscular needle placement will be assessed as a PSRM-positive verification when the needle moves upon passive stretching and relaxing of the intended muscle. Manual intramuscular needle placement will be defined as a PSRM-negative verification when there is no movement or only a small straight movement of the needle upon passive stretching and relaxing of the muscle (see Figure 1). Whether or not the needle is positioned correctly, it will at this stage not be removed or repositioned.

**Figure 1 F1:**
[figure not shown]
**Flowchart for the protocol for manual intramuscular needle placement checked by PSRM.** Manual intramuscular needle placement checked by PSRM will be assessed as a PSRM-positive verification when the needle moves upon PSRM. Manual intramuscular needle placement will be defined as a PSRM-negative verification when there is no movement or only a small straight movement of the needle upon PSRM.

The needle location will then be verified by means of a Stimuplex HNS 12 electrical stimulator. ES will be initiated at 1.50 mA. A palpable and visible contraction of only the target muscle will be assessed as an ES-true verification. The ES level will be reduced to 1.00 mA if more than one muscle contracts at the same time. If only the target muscle shows a palpable and visible contraction after the ES level is reduced, the needle location will be defined as an ES-true verification. Contraction of a different muscle will be assessed as ES-false verification. When there is no contraction at all, the current will be increased to a maximum of 5.0 mA. If there is still no muscle contraction or a different muscle contracts, or many muscles contract at the same time, this will be defined as an ES-false verification. A palpable and visible contraction of only the target muscle is defined as an ES-true verification (see Figure 2). After this procedure, regular BTX-A treatment will be continued and the needle can be readjusted if necessary.

